#### eConsult Intervention

The EHR-embedded eConsult system provides a streamlined and timely consultative process that has been shown to improve the quadruple aim-related outcomes and to enhance communication and coordination of care between primary care providers and specialists regarding specific patient areas of concern [27]. The PCP sends a focused question with relevant subjective and objective patient information to a specialist through the eConsult system. The specialist then reviews pertinent information from the EHR and responds to the PCP with guidance and care support with recommendations regarding diagnosis, treatment, and follow-up plans.

Following the patient-specific interaction with the PCP in the diabetes-specific visit, an eConsult with different specialties (indicated above) will be placed through the EHR. The eConsult system is already an established part of routine clinical care since it is embedded in the EHR. eConsults will be used to assist with clinical decision-making and obtaining specialized knowledge and support from various health care professionals based on the specific source of DD. If the patient requires additional support, the eConsult system will allow for a conversion to an in-person or telemedicine visit with the needed specialty.

#### Poststudy Intervention

Poststudy time point 1 (3 months following initial screening): the research assistant (RA) will send patients a link to complete the screening measures through the patient portal. The screening measures completed at 3 months post screening will assess for DD, symptoms of depression and anxiety, and technology use (refer to Table 1). Outside the clinical setting, the PHQ-8 will be administered instead of the PHQ-9 [28]. The technology measures include the Usability Metric for User Experience-lite (UMUX-lite) [23], System Usability Scale (SUS) [24], technology use assessment, AI chatbot system performance metrics, and eConsult system performance metrics. Qualitative data will be collected at 3 months post screening. Table 1 includes the measures and time points for data collection. The RA will call each patient to conduct a semistructured interview and ask survey questions if patients have not completed surveys electronically within 1 week. The qualitative interview will include questions about participating in screening for DD, experience with the AI health care chatbot and being referred to specialty providers through eConsults. Further, the RA will obtain qualitative data through semistructured interviews and survey questions with 6 clinical staff and both primary care providers who participated in the study. The questions for health care staff or providers will assess their time spent and experience implementing workflows that screen for DD and offer treatment options through provider support, AI health care chatbot, and eConsults.

Poststudy time point 2 (6 months following initial clinic visit): the RA will send patients a link to complete the screening measures through the patient portal at the 6-month time point. The screening measures completed at the 6-month time point are included in Table 1. If patients do not complete the surveys electronically within 1 week, the RA will call to follow up and administer surveys via phone.

### Study Design

We propose a pilot clinical trial to be conducted at a suburban multidisciplinary family medicine practice in an academic medical setting. The study is designed to provide feasibility and acceptability data for the development of DD-based screening and treatment using digital and clinical interventions.

### Participants

Up to 30 adult English- or Spanish-speaking patient participants with a diagnosis of type 1 diabetes or type 2 diabetes who receive their diabetes care from 2 PCPs at the primary care practice will be enrolled in the study. For Spanish-speaking participants, Qualified medical interpreters are used for translation services that are provided at no cost at the clinic. Qualified medical interpreters are part of routine medical services. A sample size of 30 is the minimum generally recommended if the underlying population is expected to have a normal distribution [29]. It is also double the minimum recommended number of persons to be included in human factors and usability testing for medical devices, which allows for loss to follow-up or nonparticipation by some individuals in data collection activities [30].

Clinic staff engaged in the new workflows for DD will also be invited to participate in surveys and interviews about their experience with the technology-supported intervention following the completion of the study. Inclusion and exclusion criteria are mentioned in Textbox 1.

Inclusion and exclusion criteria.
**Inclusion criteria**
Age at time of consent 18-89 years;Diagnosed with type 1 or type 2 diabetes;Patient at the primary care clinic;Able to understand English or Spanish;Willing and able to sign the informed consent form;Willing to be contacted by the study team through the patient portal, phone, or text to complete study measures;Ability to reliably send and receive text messages.
**Exclusion criteria**
Participation in another study that might interfere with participation in this study;Unable to follow the study procedures for the duration of the study or is deemed unacceptable to participate in the study per principal investigator judgment;Participant or participant’s immediate family member is an employee of the health care chatbot company providing services for the study;Planning to move in the next 6 months;Planning to change primary care practices in the next 6 months.

### Data Collection and Outcome Measures

Both qualitative and quantitative methods will be used to assess study outcomes at the patient level, practice level, and technology system level. Patient-level health outcomes include DD, depression, and anxiety measured at baseline, 3 months, and 6 months using the T1-DDAS or T2-DDAS, PHQ-8, and GAD-7. The T1-DDAS was selected to be used in this study because it is the most updated and comprehensive assessment tool for determining DD in people with type 1 diabetes. The T2-DDAS was used as a measure because it is the most comprehensive and contemporary survey tool to determine DD among people with type 2 diabetes. The PHQ-9 and GAD-7 are commonly used brief screeners in primary care [21,22]. User experience with technology will be assessed through the administration of the UMUX-lite at 3 months, the SUS at 3 months, and a technology use assessment at baseline and 3 months. The SUS is widely adopted as a reliable measure of usability across technology types and in a variety of populations. The UMUX-lite represents a user experience-focused usability measure that has proven to correlate well with the SUS in overall usability and is appropriate for use with health technologies. The technology use assessment was previously developed by a member of the research team for use in discerning technology adoption and use patterns with primary care patients [25]. In addition, qualitative data from interviews and responses to open-ended survey items will be collected from practice staff, PCPs, and patients to determine the acceptability and feasibility of implementing screening and technology-supported treatment for DD. Interviews will be conducted by a trained qualitative analyst according to a semistructured interview guide, recorded and transcribed using artificially intelligent transcription software (Otter.ai), with human adjudication of transcripts to avoid error (refer to Multimedia Appendices 1 and 2 for interview guides). Positive experiences with the digital interventions will be determined by participant responses to the qualitative interview questions. Further, PCPs will complete the DD Provider Time Survey to track activities and time spent on workflow tasks. Acceptability with the eConsults will be evaluated by standard data collection protocols in the EHR. eConsult data will capture the patient-specific inquiries and requests from PCPs and responses given by specialists. AI chatbot performance data will be collected from the chatbot system and used to evaluate engagement with the AI chatbot according to the People at the Center for Mobile Application Design framework [31]. Table 1 lists the measures to be collected for this study in detail.

A number of the validated measures have existing published versions in both English and Spanish including the T1-DDAS, T2-DDAS, PHQ-8, and GAD-7. For outcomes measures including the UMUX-lite, SUS, and the technology use assessment that did not have an available version in Spanish, we had a system-verified language translator assist in translating these materials from English into Spanish.

### Data Analysis

#### Quantitative Data Analysis

The study team will use standard statistical packages (eg, R [R Foundation for Statistical Computing]) to conduct data analysis. Descriptive statistics (means, SD, frequency distributions, and proportions) will be used to summarize baseline patient characteristics, clinical and behavioral outcomes, and other quantitative outcome measures and responses to closed-ended survey items. As a feasibility study, it is not powered for inferential analyses or power analyses, but the results are expected to inform future work. Based on results from similar studies, a 60% (18/30) threshold will be used to determine technical and operational feasibility and user acceptability, that is, 60% (18/30) of participants remain engaged with the technology solutions throughout the duration of the study, and 60% (18/30) of participants report positive experiences and satisfaction levels with the program overall [32]. The study has been planned to minimize the amount of missing data overall and thus anticipates the use of maximum likelihood methods to estimate missing values for statistical analysis. We will use this data to calculate an effect size to power a larger study.

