### Objective and Aims

The primary objective of this study is to assess the feasibility and accessibility of using health IT integrated into primary care workflows to improve screening and treatment for DD. This project will examine the technical and operational feasibility, patient and provider experience, and behavioral health outcomes of a new technology-supported workflow to conduct screening for DD and provide follow-up treatment by a multidisciplinary team in a primary care setting.

The aims of this pilot study are to (1) design and implement individualized technology-supported DD workflows, (2) evaluate the acceptability and integration of technology-based workflows to provide treatment for DD, and (3) evaluate the change in DD (baseline, 3 months, and 6 months) in patients receiving screening and personalized treatment for it. Symptoms of anxiety and depression will also be evaluated. The primary outcome of this study is to determine the feasibility and acceptability of integrating individualized workflows for DD into primary care.

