
#### AI Chatbot Intervention

All patient participants, regardless of whether they have DD or the severity of the DD, will be enrolled to receive text messages from the AI chatbot. The AI chatbot will provide education on DD, normalization of DD, suggestions for solution-focused coping strategies, and information provision on patient resources and support. For patients not reporting symptoms of DD, chatbot messaging will be seen as a preventative measure to provide information and build awareness of DD should this arise in the future. For patients reporting DD, the AI chatbot will be seen as a resource to provide suggestions for coping strategies connecting to local support resources and psychoeducational material. Following a collaborative discussion with their PCP on the sources of DD that they would like to receive support on, they will obtain a push notification with the top 3 identified areas of distress. Following this initial conversation, the AI chatbot will deliver a 12-week curriculum on topics specifically related to DD and the sources of DD (for either the T1-DDAS or T2-DDAS). Participants will receive 3 scheduled text messages on the curriculum content per week throughout the 12 weeks to their cell phone. In between scheduled messages, participants can initiate interaction with the AI chatbot through the text message chain if they choose. Development of the AI chatbot content was overseen and reviewed by DD expert consultants. Participants will not receive messages on topics unrelated to DD or content that was not developed and approved by the study team. In other words, participants will not receive content that is generated by the system or off-topic.

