A potential limitation of eConsult use is the increased, noncompensated workload on primary care providers, who must act on the e-consultant’s recommendations for each patient. Primary care is a fast-paced setting that is often stretched for resources, staffing, and time. Further, primary care is a diverse setting with varied access and structures to care delivery. Consequently, it is unlikely that a single approach or method of care is appropriate in all primary care settings. With significant variability in primary care, interventions need to have adequate flexibility to have a chance to be incorporated successfully into this care environment. Feasibility studies offer an opportunity to determine if interventions can be flexibly disseminated into primary care in a scalable fashion. For the AI chatbot, we anticipate a limitation to be the imperfect matching of responses to participant questions. We are mitigating this limitation by setting expectations upfront with participants and using the dataset to iteratively improve chatbot responses over time with use. We chose this curated content route versus an open generative AI approach to minimize potential risks from chatbot hallucination or inaccurate responses.

Given that this is a feasibility study with a small sample size, and we are not powered for inferential analyses, the results of this study will not be generalizable. However, the results of this study will be used as preliminary data for a larger trial.

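### The plan to power a larger study on an effect size from this pilot rests on an uncontrolled within-person change in at most 30 patients, which cannot fix a sample size

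*Protocol article*

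**What the plan says.** The commitment is in the protocol article, Quantitative Data Analysis: "We will use this data to calculate an effect size to power a larger study". Earlier in the same paragraph stands: "As a feasibility study, it is not powered for inferential analyses or power analyses, but the results are expected to inform future work". Limitations and Challenges adds that "the results of this study will be used as preliminary data for a larger trial".

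The design features that decide what kind of effect size is available are these:

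- **Size.** Participants: "Up to 30 adult English- or Spanish-speaking patient participants with a diagnosis of type 1 diabetes or type 2 diabetes". The reason given is a rule of thumb ("A sample size of 30 is the minimum generally recommended if the underlying population is expected to have a normal distribution") together with a doubled usability-testing minimum, "which allows for loss to follow-up or nonparticipation by some individuals in data collection activities". No retention rate is given.
- **Allocation.** Everyone gets the chatbot's messages, as the AI Chatbot Intervention section states: "All patient participants, regardless of whether they have DD or the severity of the DD, will be enrolled to receive text messages from the AI". No comparison group is described anywhere.
- **Contrast.** Objective and Aims: "evaluate the change in DD (baseline, 3 months, and 6 months) in patients receiving screening and personalized treatment for it".
- **Instruments.** Table 1 gives the T1-DDAS (30 items) for type 1 diabetes and the T2-DDAS (29 items) for type 2.

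**The concern.** Where every participant is treated and DD is measured before and after, the data yield a within-person change. That change contains whatever the intervention did, plus whatever would have happened over 3 or 6 months anyway: time trend, changes in usual care, and the effect of being asked about distress. A controlled trial is sized on a difference between groups, and this design cannot estimate one.

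Two features blur a single figure further. Patients who screen negative for DD are included and have little room to improve. The outcome also comes from two different scales.

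Aside from bias, 30 patients or fewer give a wide interval. The larger study's sample size could then be far too small or far too large, depending on where the pilot estimate happens to fall.

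**Working it through.** **The plan's own figure.** The sample size of 30 cannot be reproduced, because it comes from rules of thumb with no alpha, power, effect size, SD or dropout rate. No effect size is stated either. Everything below is therefore an illustration over assumed values.

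**Inputs.** From the document: n at most 30, one group, paired measurements. Assumed: DD is the outcome to be powered; observed paired standardized change d of 0.3, 0.5 or 0.8; 30, 24 or 18 patients with paired data; a later 1:1 two-arm trial with 80% power and 5% two-sided alpha.

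**Step 1: precision.** With t = d × √n on n - 1 degrees of freedom, the noncentral t distribution is inverted for the 95% limits of the noncentrality, and these are divided by √n.

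**Step 2: later sample size at face value.** n per arm = 2 × (1.96 + 0.8416)² / d² = 15.70 / d², rounded up. For d = 0.5: 15.70 / 0.25 = 62.8, so 63. For d = 0.3: 15.70 / 0.09 = 174.4, so 175.

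| Pairs | Assumed d | 95% CI | Per arm at d | Per arm across the CI |
|---|---|---|---|---|
| 30 | 0.3 | -0.07 to 0.66 | 175 | 36 to no finite number |
| 30 | 0.5 | 0.12 to 0.88 | 63 | 21 to 1165 |
| 30 | 0.8 | 0.38 to 1.21 | 25 | 11 to 108 |
| 24 | 0.3 | -0.11 to 0.71 | 175 | 32 to no finite number |
| 24 | 0.5 | 0.07 to 0.92 | 63 | 19 to 3195 |
| 18 | 0.5 | 0.00 to 0.99 | 63 | 17 to effectively unbounded |

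Sample sizes use unrounded limits.

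**Step 3: no comparator.** Suppose 25% or 50% of an observed 0.5 would have occurred without the intervention (assumed shares). The true difference is then 0.375 or 0.25. A trial of 63 per arm has power Φ(δ × √(63/2) - 1.96), which is 56% or 29% and not 80%. The numbers needed would be 112 or 252 per arm. The pilot cannot say what the share is.

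**Step 4: scale.** A paired d is in units of the SD of change. In raw-score SD units it is d × √(2(1 - r)), where r is the baseline/follow-up correlation and the two SDs are taken as equal.

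- r = 0.7: 0.5 × √0.6 = 0.39, so 15.70 / 0.15 = 104.7, or 105 per arm.
- r = 0.8: 0.5 × √0.4 = 0.32, so 15.70 / 0.10 = 157.0, or 157 per arm.

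These two figures apply if the later trial compares follow-up scores without baseline adjustment. The 63 applies if it compares change scores. With baseline adjustment the factor (1 - r²) enters, giving 104.65 × 0.51 = 53.4 (54 per arm) or 156.98 × 0.36 = 56.5 (57 per arm). So even with the point estimate held fixed, the answer runs from 54 to 157 according to r and the analysis.

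**Step 5: what the pilot can estimate better.** The 95% CI of an SD at n = 30, from the chi-square distribution, is 0.80 to 1.34 times the estimate, so the implied sample size varies by a factor of 0.63 to 1.81. That is about a threefold span (1.81 / 0.63 = 2.9), against about 55-fold for d = 0.5 (1165 / 21). Each DDAS instrument will have fewer than 30 patients if both types are enrolled. At n = 18 the SD interval is 0.75 to 1.50 times the estimate.

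**The case against.** The strongest reply is that this is a pilot whose primary outcome is feasibility and acceptability. Limitations and Challenges already says it is small, not powered for inference and not generalizable. Neither section gives the design of the larger study, and the full protocol may say how the effect size would be combined with an interval or an important difference. Much of this stands. The two-arm design above is an assumption, and the impact falls on a later study. It does not remove the point, because the article makes a positive commitment, and informing the larger study is one of its stated purposes.

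Three stronger readings are tempting, and the document does not support them.

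- **Internal contradiction.** A reader might infer that the paragraph declares the study unfit for power analyses and then promises one. The sentence more naturally means that no power calculation lies behind the pilot, and its second half already looks ahead to future work. The wording is loose, no more.
- **Regression to the mean.** A reader might expect it to inflate the change. Eligibility does not depend on distress, and patients enter whatever their DD level, so the expected whole-sample effect is about zero. It would matter in a subgroup chosen for high baseline scores, but no such effect size is planned.
- **A doomed later trial.** Nothing shows that the larger study will in fact be underpowered or abandoned. The document has no rule for dropping it, and the error could go either way.

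**Conclusion.** The point holds as a moderate one. The effect size that this design can deliver is an uncontrolled within-person change, and it is too imprecise to set a sample size. The size of the problem depends on the observed effect, which is unknown: at an assumed 0.3 the interval includes zero, while even at an assumed 0.8 with full retention the implied size runs from 11 to 108 per arm. The lack of a comparator and the paired scale add uncertainty that a confidence interval does not show. The per-arm figures rest on an assumed two-arm trial and the stated alpha and power; the conclusion about precision does not. The 60% feasibility and acceptability assessment is unaffected.

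**What to change.** Replace the last sentence of the Quantitative Data Analysis paragraph with a statement to this effect:

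- The pilot will supply, each with a 95% CI, the SD of each DDAS core score, the baseline/follow-up correlation, retention at 3 and 6 months, the recruitment rate and the prevalence of each distress level.
- Any controlled larger trial will be powered on a minimally important between-group difference, justified separately, and not on the change observed here.
- The observed change in DD will be reported with its 95% CI and labelled as uncontrolled.

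At the same time, reword the phrase about not being powered for power analyses so that it says plainly that no power calculation underlies the sample size of 30.

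The cost is a sentence or two of text and no new data. The pilot gives up its claim to an effect size, and the team must find and defend an important difference, which the document does not give.

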#### Qualitative Data Analysis

This study’s acceptance is determined by patient and health care provider user experience through interviews, clinical team member feedback, and responses to user experience surveys. An overall positive rating on tailored survey items or positive themes identified from qualitative data represents acceptability for this study. The program will be deemed acceptable among participants overall if 60% (18/30) or more of participants report positive ratings and themes. Qualitative analysis of open-ended survey data and interview data will be conducted using rapid thematic and content analysis to assess user experience by identifying and exploring common topics and themes that emerge from participants’ responses. The rapid analysis will be informed by the Consolidated Framework for Implementation Research and will use a dual-read approach and matrix classification method with 2 reviewers, who will discuss classification decisions to achieve consensus [33]. Enough participants are included in the planned sample size to ensure qualitative analyses will reach thematic saturation overall.

